### Longitudinal analyses

QoL will be described at each follow-up and then longitudinally analyzed using a mixed model analysis of variance for repeated measurements to investigate and test a time trend for QoL [39-41]:

These models will have to take into account non-random missing data.

With simple imputation methods for sensitivity analyses:

Mean QoL score imputation: Means will be calculated for the whole population and for specific patient profiles (cancer location, age, sex, and so on) at each follow-up and then will be imputed for patients with missing QoL scores

Extreme QoL score imputation. This method could be used when the missing data are due to a pejorative event such as death or disease progression.

With 'pattern mixture' models [42,43]:

Qualitative variables will be created to describe missing QoL score profiles and to define patterns for these analyses (no missing score, intermittent and drop-out profiles).

Time until definitive QoL score deterioration:

Analyses of time until a definitive QoL score deterioration (TUDD) will be estimated using the Kaplan-Meier method [44].

The TUDD of a score will be defined as the time interval between randomization and the first decrease in the MCID score ≥ 5 points compared to the QoL score at inclusion with no further improvement in QoL score ≥ 5 points or in the case of patient who dropped out after a ≥ 5-point decrease, resulting in missing data.

Patients will be censored at the last QoL follow-up when no ≥ 5-point deterioration in the QoL score from baseline will be observed or for patients with a ≥ 5-point deterioration, but with a subsequent ≥ 5-point improvement as compared to baseline QoL score.

Patients with no available QoL scores will be included in the TUDD analysis, but censored immediately.

2. To assess the impact of therapeutic strategies on QoL at the end of life Since treatments and care strategies will be longitudinally collected, for exploratory purposes only, we will compare longitudinal QoL according to these strategies using mixed model analysis of variance and Log Rank tests and Cox models for the time to definitive QoL deterioration analyses.

QoL will be described at each follow-up and compared at the inclusion (using Wilcoxon rank test) and then longitudinally analyzed using mixed model analyses of variance for repeated measurement [39-41] to test for the following: a therapeutic strategy effect whatever the follow-up; time effect whatever the therapeutic strategy; interactions between therapeutic strategy and follow-up; and effects of other clinical factors. The best model will be chosen according to the smaller Akaike's information criterion (AIC).

As for the TUDD approach, it will be compared with Log-Rank tests. Univariate and multivariate Cox analyses will be done to compute hazard ratios with 95% CI.

3. To assess the added value of spontaneous QoL completion to detect a clinically significant change in this setting

The proportion of patients who report at least one MCID during follow-up using the Jaeschke transition question will be compared according to the group allocated by randomization using univariate and multivariate logistic regressions.

We will also compute effect size (ES) and standardized response mean (SRM) to explore sensitivity to change according to spontaneous completion of a QoL questionnaire or not. We aim to demonstrate that with spontaneous completion of QoL questionnaires, ES and SRM will be improved.

For the sensitivity analysis, time to definitive QoL deterioration will also be estimated including this spontaneous completion of QoL questionnaires.

Analyses will be performed on an intent-to-treat principle.

4. To assess the effect of questionnaire order on QoL levels Longitudinal QoL analyses will be done as described above QoL will be described at each follow-up and compared at inclusion and then longitudinally analyzed using the mixed model analysis of variance for repeated measurements [39-41]. For the TUDD approach, it will be compared with Log-Rank tests. Univariate and multivariate Cox analyses will be done to compute hazard ratios with 95% CI.

Analyses will be performed on an intent-to-treat principle.

5. To define a period of 'end of life' QoL dimensions that strongly correlate with a patient's health status (physical dimensions, fatigue, pain) should decrease at the end of life, whereas dimensions (psychological, spirituality) more related to the end of life could remain stable and/or could slowly improve. These patterns in longitudinal QoL changes will be captured using mixed model analysis of variance for repeated measurement, and time until definitive QoL score deterioration.

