#### Secondary objectives

1. To longitudinally assess QoL of cancer patients until death using QLQ-C15 PAL, the French version of QUAL-E, and of Missoula Vitas Quality of Life Index (MVQOLI) Statistical analyses will be conducted to investigate longitudinal changes of each QoL dimension: description of missing QoL scores; missing QoL questionnaires and scores will be studied and classified according to Diggle and Rubins' method to determine whether the missing data were random or not: Missing Completely At Random, Missing At Random, Missing Not At Random [30,31,37,38].

Univariate and multivariate Logistic regression will be done to construct a clinical model to predict missing QoL and to investigate the random nature of missing QoL data. The numbers of missing scores will be described according to the patient subgroups and compared using ANOVA and Mixed Anova for repeated measurement.

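### Single mean imputation is a poor sensitivity analysis for non-random missing QoL scores: it assumes more than the mixed model, understates standard errors and can flatten a real decline

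*Protocol article*

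**What the plan says.** In the protocol article, Longitudinal analyses, QoL is to be "longitudinally analyzed using a mixed model analysis of variance for repeated measurements to investigate and test a time trend for QoL". The next sentence sets a requirement: "These models will have to take into account non-random missing data". Three methods follow.

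- **Mean imputation**, introduced by "With simple imputation methods for sensitivity analyses". "Means will be calculated for the whole population and for specific patient profiles" (an open-ended list that names cancer location, age and sex) "at each follow-up and then will be imputed for patients with missing QoL scores".
- **Extreme-score imputation**, under the same line but optional: "This method could be used when the missing data are due to a pejorative event such as death or disease progression".
- **Pattern-mixture models**, with patterns for complete, intermittent and drop-out profiles.

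No multiple imputation or variance correction is attached to the mean imputation.

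Item 1 under Secondary objectives plans to classify missing data as MCAR, MAR or MNAR. Logistic regression is to be used to predict missing QoL and "to investigate the random nature of missing QoL data".

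**The concern.** A sensitivity analysis is useful when it relaxes an assumption of the main analysis. A likelihood-based mixed model on the observed scores is valid under MAR because it uses each patient's earlier scores. Filling a gap with the visit mean discards those scores, so it needs missingness to be close to completely random within the profile. That is a stronger assumption, so the check cannot speak to non-random missingness. Treating filled values as observed also makes the standard errors too small.

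The article itself expects missingness to be linked to health. Completion of QoL questionnaire foresees patients too ill to answer and follows patients monthly until death, and Longitudinal analyses names death and progression as causes of missing scores. Patients who still answer are then likely to be the healthier ones, and giving their mean to the others can hide a decline. This matters for secondary objective 5, which relies on telling declining dimensions from stable ones, and for objective 4, which reuses the longitudinal analyses.

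A smaller, related point concerns the planned classification. Observed data can contradict MCAR, but they cannot separate MAR from MNAR.

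**Working it through.** The article gives no missing rate, SD or standard error for this analysis, so there is no figure to reproduce. From the article: N = 372 and monthly assessments. Everything else below is an assumption.

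**1. Standard error of a visit mean.** Let n patients be due, a share r have a score, and s be the SD of the observed scores.

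- Filling with the observed mean adds no squared deviation, so the variance of the filled data is about r·s².
- Naive SE = s·√(r/n). Available-case SE = s/√(r·n). Their ratio is r.
- Coverage of a nominal 95% interval with no bias = 2Φ(1.96·r) − 1.

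With n = 372 and assumed s = 20:

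| Completion r | Naive SE | Available-case SE | Ratio | Coverage |
|---|---|---|---|---|
| 0.80 | 0.93 | 1.16 | 0.80 | 88% |
| 0.60 | 0.80 | 1.34 | 0.60 | 76% |
| 0.40 | 0.66 | 1.64 | 0.40 | 57% |

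A simulation of one visit under MCAR (4,000 runs) agrees: coverage was 92%, 88%, 79%, 66% and 44% at 10%, 20%, 34.6%, 50% and 70% missing.

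**2. Level at a single visit.** The mean of the filled data equals the mean of the observed scores. If non-responders score lower, the visit mean is too high, but by exactly the bias of the available-case mean. Imputation adds nothing here, so this is not counted against it.

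**3. Time trend, the quantity the plan tests.** The simulation used 372 patients, four monthly visits, a true slope of −5.0 points per visit, random intercepts and slopes (SD 14 and 4), residual SD 10 and 100 runs. Dropout depended on the previous score (MAR) or on the current score (MNAR). Missing shares at visits 2 to 4 were 23%, 43% and 59% under MAR, and 30%, 52% and 66% under MNAR. Filling used the whole-population visit mean.

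| Dropout | Analysis | Mean slope | Model SE | Empirical SD |
|---|---|---|---|---|
| MAR | Mixed model, observed scores | −4.98 | 0.48 | 0.52 |
| MAR | Mixed model after mean imputation | −1.55 | 0.31 | 0.50 |
| MNAR | Mixed model, observed scores | −1.90 | 0.46 | 0.49 |
| MNAR | Mixed model after mean imputation | +0.14 | 0.30 | 0.53 |

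Under MAR, mean imputation spoils an estimate that was right. Its model SE of 0.31 is the same as that from complete data with nothing missing (0.31), although up to 59% of scores were filled in. Under MNAR the mixed model is itself biased, so a method that addresses MNAR is still needed, but mean imputation moves further from the truth.

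Profile means were not simulated. Profiles of cancer location, age and sex would help only as far as they predict the missing score. They do not carry the patient's earlier QoL or health status.

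**The case against.** The strongest reply is that mean imputation is one method of three. Extreme-score imputation targets loss through death or progression, and pattern-mixture models can address drop-out that is not at random. Mean and extreme imputation might also be read as bracketing the result. This stands in part. A reader might infer that the plan has no MNAR check, and the article does not support that. However, the extreme-score method is only optional, and neither companion corrects the standard errors or the trend from the mean-imputed analysis.

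A reader might also infer that mean imputation would falsely confirm the main model. The simulation shows the reverse: the two results disagree, −1.55 against −4.98 under MAR. The risk is a misleading discrepancy, with too small a standard error attached to the worse estimate.

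Nor is an optimistic bias established for every dimension. Objective 5 expects psychological and spiritual dimensions to stay stable or slowly improve, and proxy help and recorded reasons for non-completion should limit and explain missing data.

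On the classification, no analysis is made conditional on the label, and the requirement to handle non-random missing data is unconditional. What remains is the wording about what logistic regression can show.

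Finally, a statistical analysis plan is promised before database lock and may settle details. But filling with observed means is a method the article states, not a detail it leaves open.

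**Conclusion.** The point holds as a limited one. Single mean imputation cannot test non-random missingness, because it assumes more than the mixed model it is meant to stress. The understated standard error follows from the method under any missingness mechanism; for a visit mean the factor is about r. Flattening of a decline requires missingness linked to poor health, which the article anticipates. Its size here (−5.0 to −1.55 under MAR) rests on the assumed slope, variances and dropout and is illustrative only.

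The reach is a sensitivity analysis for secondary longitudinal objectives. The test-retest ICC and the comparison of the proportion of patients reporting an MCID do not use it. A change is worthwhile because it is cheap and removes a result that could mislead.

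**What to change.** 1. In Longitudinal analyses, replace mean imputation with multiple imputation that uses prior scores, performance status and PPS. Table 1 already schedules these at each follow-up.
2. Add delta shifts for scores missing while the patient is alive because of deterioration, scaled to each instrument: for example 0, 5% and 10% of the theoretical range, in line with the 5% MCID in Sample size for secondary objectives. On a 0–100 scale these are 0, 5 and 10 points. By the article's formula each MVQOLI dimension runs from −30 to +30 ((2 + 4) × 5 = 30), so the total runs from 0 to 30 (±150/10 + 15) and the shifts are 0, 1.5 and 3 points. A flat 10-point shift would be a third of that range.
3. Keep the pattern-mixture models.
4. In Secondary objectives, item 1, state that the logistic models can contradict MCAR and describe predictors of missingness but cannot separate MAR from MNAR.

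The cost is revised wording and slightly more analysis work with standard software. No new data collection is needed.

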### Recruitment

Once eligibility criteria have been checked, patients from French comprehensive cancer care centers or hospitals will be invited to join the study.

Before inclusion, patients should read and understand the study information letter and then should date and sign the informed consent form (ICF) to allow them to join the study.

The coordinating center will be notified of each inclusion before completion of the first QoL questionnaire (inclusion document will be completed and returned to Paul Papin Center, Angers by fax).

Since eligibility criteria will be checked and patients' ICF will be collected, the first QoL questionnaires and the test-retest (3 days after the first completion) will be completed (before randomization) in the following order: QLQ-C15 PAL, MVQOLI, and QUAL-E.

After completion of the retest QoL questionnaire, the eligibility criteria and date of signed informed consent will be collected on a dedicated internet site to allow e-randomization with a personal log-in and password (Tenalea software). The study coordinator will then be able to randomize patients. The allocated arm will be sent to investigators, to the methodologists, the principal investigator and the coordinating center by email.

Patients will be randomized after the test-retest to limit the number of non-assessable patients for reproducibility.

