### Completion of QoL questionnaire

The QoL questionnaires will be completed before randomization and then every month until death in a time driven design fashion.

Using test-retest methodology, the QLQ-C15 PAL, MVQOLI, and QUAL-E questionnaires will be completed 3 days after the first completion at baseline and before randomization [27].

Though a maximum delay of 15 days is usually allowed between completions to check reproducibility, since these patients have a specific end-of-life profile with sometimes a rapid deterioration in general health status, a maximum delay of 3 days was chosen to minimize the 'risk' of changes in health status.

Since the QUAL-E questionnaire should be completed using a direct interview; patients should complete it last to prevent social desirability bias on QLQ-C15 PAL and MVQOLI evaluations [27].

In order to prevent missing QoL data [28], if a patient is unable to complete questionnaires due to poor health status, QLQ-C15 PAL and MVQOLI could be completed with the help of a proxy (from the medical team) who will have to record the patient's answers without interpretation [29]. A specific item will be completed to take this information into account for the longitudinal analysis of QoL.

All patients will complete QoL questionnaires every month until death.

In arms C and D, depending on patients' health status or perceived QoL, patients will be free to complete the QLQ-C15 PAL and MVQOLI questionnaires (spontaneous QoL completion in an event drive design) between two planned evaluations. A patient CRF including QLQ-C15 PAL and MVQOLI questionnaires, the date of completion, the perception of QoL changes using the Jaescke transition question [30]), and a space for free comments will be created. This booklet will be given to the patients after randomization.

The QoL questionnaires will be administered in a homogeneous way by the same person, a nurse specialized in palliative care, a psychologist, or if necessary a clinical research assistant (CRA), throughout the patient follow-up until death.

Completed questionnaires should be returned to one of the CRAs assigned to the study. In order to deal with holidays, a minimum of two full-time CRAs will be required and identified for each participating center (Table 2).

**Table 2 T2:** Center's participation agreement

Organization	City
Cancer care center Paul Papin	Angers, France

Cancer care center Léon Bérard	Lyon, France

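### Time until definitive deterioration is judged against one inclusion score, although a second pre-randomization score exists that could make the reference less noisy

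*Protocol article*

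**What the plan says.** In the section Longitudinal analyses, the definition begins "The TUDD of a score will be defined as the time interval between randomization and the first decrease", and the decrease is measured as "the first decrease in the MCID score ≥ 5 points compared to the QoL score at inclusion". The event must also be definitive: "with no further improvement in QoL score ≥ 5 points or in the case of patient who dropped out after a ≥ 5-point decrease". The censoring rule uses another term for the reference: patients are censored if they deteriorate but "with a subsequent ≥ 5-point improvement as compared to baseline QoL score".

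Two full assessments precede the clock. Under Completion of QoL questionnaire, all three "questionnaires will be completed 3 days after the first completion at baseline and before randomization". Under Recruitment, "Patients will be randomized after the test-retest". The same section says "The coordinating center will be notified of each inclusion before completion of the first QoL questionnaire", which points to D1 as the score at inclusion. Table 1, however, places D1 and the retest together under Baseline, and a footnote allows the retest later on the same day as D1. The statistical section uses the retest for the ICC and the Bland-Altman graph. It gives it no role in TUDD.

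**The concern.** The reference score is older than the start of the clock, its name differs between the event rule and the censoring rule, and the score nearest to randomization is left unused. A single score includes measurement error. A patient whose D1 score happened to be high tends to fall at follow-up without any real decline, and one whose D1 score happened to be low can decline without being detected. With a threshold of only 5 points, this error decides many events.

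TUDD serves secondary objectives 1, 2, 4 and 5, and is a sensitivity analysis for objective 3. It also feeds the attempt to define an end-of-life period, where false events enter the Kaplan-Meier curve directly.

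**Working it through.** The article gives no sample size, power or event rate for TUDD, so there is no planned figure to reproduce.

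**Inputs**
- Threshold of 5 points (Longitudinal analyses).
- QLQ-C15 PAL scores from 0 to 100 (End of life QoL questionnaires).
- Minimum acceptable ICC of 0.65 (Primary objective analyses).
- Between-patient SD: not given. Assumed 15 to 30 points.
- Model: normal scores, independent errors, patient truly unchanged. Error variance of one score: e = SD² × (1 − ICC).

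**1. Retest against D1 in stable patients.** The SD of the difference is SD × √(2(1 − ICC)). For SD 20 and ICC 0.65 this is √280 = 16.7, so P(retest at least 5 below D1) = Φ(−5/16.7) = 0.383.

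| SD | ICC 0.65 | ICC 0.90 |
|---|---|---|
| 15 | 0.345 | 0.228 |
| 20 | 0.383 | 0.288 |
| 25 | 0.406 | 0.327 |
| 30 | 0.421 | 0.355 |

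These patients stand below the threshold when the clock starts. They are not events. They are, however, more likely to become events: in a simulation of stable patients at SD 25 and ICC 0.65, 60% of them were at least 5 points below D1 at the first follow-up, against 27% of the others.

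**2. Error variance of change from baseline.** With D1 alone it is e + e = 2e. With the mean of D1 and retest it is e + e/2 = 1.5e. The reduction is 0.5/2 = 25%, and the SD falls by 1 − √0.75 = 13%. If the D1 and retest errors correlate at ρ, the variance becomes e + e(1 + ρ)/2, and the reduction is 25% × (1 − ρ). At ρ = 0.5, for example, it is 12.5%.

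**3. False drop of at least 5 points at one follow-up, stable patient.** With the mean as reference, the probability is Φ(−5/(SD × √(1.5(1 − ICC)))).

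| SD, ICC | D1 alone | Mean of two | Difference (points) |
|---|---|---|---|
| 15, 0.65 | 0.345 | 0.323 | 2.2 |
| 20, 0.65 | 0.383 | 0.365 | 1.8 |
| 25, 0.65 | 0.406 | 0.391 | 1.5 |
| 30, 0.65 | 0.421 | 0.409 | 1.2 |
| 20, 0.90 | 0.288 | 0.259 | 2.9 |

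Simulating definitive deterioration over 1 to 4 follow-ups gave the same order of gain, about 1 to 3 points. Using the retest alone as reference left the rate unchanged: it moves the reference next to time zero but does not reduce its error.

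**4. What that means for a comparison (ideal case).** Take one visit, SD 20 and ICC 0.65, with one group stable and one truly 5 points lower. The second group crosses the threshold with probability 0.500 under either reference.
- D1 alone: the difference is 0.500 − 0.383 = 0.117 and the sum of binomial variances is 0.236 + 0.250 = 0.486.
- Mean of two: the difference is 0.500 − 0.365 = 0.135 and the sum is 0.232 + 0.250 = 0.482.

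The ratio of difference² to variance rises by a factor of about 1.33 (before rounding). This is a ceiling, since true changes also vary between patients.

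**5. Scale.** By the scoring rule in the article, an MVQOLI dimension runs from (−6 × 5) = −30 to +30. The total therefore runs from −150/10 + 15 = 0 to 150/10 + 15 = 30. Five points is 5/30 = 16.7% of that range, so the probabilities above do not carry over to it.

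**The case against.** The strongest reply is that choosing the baseline record is a detail for the statistical analysis plan, which the article promises before database lock, and that a D1-only rule is nowhere stated in so many words. The second part is right: D1 is the likelier reading, not the text. The first part only partly answers the point, because the article does fix the clock, threshold, event and censoring rules, and uses two terms for the reference within them.

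A reader might infer that patients with a low retest already count as deteriorated at time zero. The document does not support this. The retest lies before the interval, the next scheduled score is about a month after randomization, and the event must be definitive.

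A reader might also extend the point to every change score. That is too wide. Effect size and standardized response mean are computed between follow-ups, the mixed models are not specified as change from D1, and the main endpoint for spontaneous completion rests on the Jaeschke question.

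Three further objections stand as limits:
- The fall in false events is small, because most of them come from a 5-point threshold set against test-retest error.
- Averaging does not remove the gap at time zero. A retest 10 or more points below D1 is still 5 or more below the mean, with probability Φ(−10/16.7) = 0.275 at SD 20 and ICC 0.65.
- Same-day retests and the one-week recall of the QLQ-C15 PAL may correlate the two errors, so 25% is an upper bound. Not every patient will have both scores.

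**Conclusion.** The point holds as an inexpensive improvement to TUDD together with a wording repair. It is not a flaw that invalidates an analysis. The reference score is not named consistently, and the likely reading leaves a second pre-randomization score unused. Using both scores lowers the error variance of change from baseline by up to 25% and false deteriorations by about 1 to 3 percentage points.

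Both baseline scores precede randomization and use one questionnaire order, so the noise is equal across randomized arms: it dilutes comparisons and does not bias them. That assurance does not extend to objective 2, whose treatment groups are not randomized.

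The figures rest on an assumed SD, a normal model with independent errors, and reliability at or above the protocol's minimum of 0.65. They apply to TUDD on 0-100 scores, not to the MVQOLI total. The primary ICC analysis is untouched.

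**What to change.** In Longitudinal analyses:
- Define the TUDD reference as the mean of the D1 and retest scores, or the available one if the other is missing.
- Use one term for it in both the event rule and the censoring rule.
- State that the retest cannot itself be an event.
- Keep D1 alone as a sensitivity analysis.

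This takes a few sentences and no new data. It can still be prespecified: at submission 12 of 372 patients were included and the analysis plan was yet to be written. The one drawback is slightly less sensitivity to a true change between D1 and the retest. The interval is at most 3 days, and the sensitivity analysis would show any such effect.

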## Methods

### Objectives

Primary objectives are: to cross-culturally adapt the English questionnaires QUAL-E and MVQOLI (Missoula Vitas Quality Of Life Index) and to validate their psychometric properties in the end-of-life setting.

Intermediate objectives are: to translate and adapt the English version of QUAL-E and MVQOLI into French taking into account cultural differences.

Secondary objectives are: to longitudinally assess QoL of cancer patients until death using the QLQ-C15 PAL, the French version of QUAL-E and the Missoula Vitas Quality of Life Index (MVQOLI); to assess the impact of therapeutic strategies on QoL at the end of life; to assess the added value of spontaneous completion of QoL questionnaires to detect a clinically significant change in this setting; to assess the effect of the order of questionnaires on QoL levels; to define a time period for the 'end of life'.

Primary outcomes for cross-cultural and psychometric validation (see also statistical methods): reproducibility of QoL scores estimated by intraclass correlation coefficients; sensitivity to change estimated by effect size and the standard error of mean; discriminant capability; and convergent validity.

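### The rule for time until definitive deterioration censors deaths without a recorded drop, and the analyses stated for objective 5 do not yield a length of time before death

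*Protocol article*

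**What the plan says.** Under Longitudinal analyses, the protocol article states: "Analyses of time until a definitive QoL score deterioration (TUDD) will be estimated using the Kaplan-Meier method". The interval is "defined as the time interval between randomization and the first decrease in the MCID score" of at least 5 points from the inclusion score, with no later improvement of that size. A patient who drops out after such a decrease also counts as an event.

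For everyone else: "Patients will be censored at the last QoL follow-up" if no drop of at least 5 points from baseline was seen. Patients whose drop was later reversed are censored too. A separate sentence reads: "Patients with no available QoL scores will be included in the TUDD analysis, but censored immediately". Death is named neither as an event nor as a competing event for TUDD. It appears only as a possible reason for extreme-score imputation, an optional sensitivity method for the mixed models.

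On follow-up, Completion of QoL questionnaire says: "All patients will complete QoL questionnaires every month until death". Under Recruitment, the baseline and retest forms are both completed before randomization.

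The last secondary objective (Objectives section) is "to define a time period for the" end of life. Item 5 of the secondary-objective analyses expects physical dimensions to fall near death while psychological and spiritual ones hold or improve. It then says: "These patterns in longitudinal QoL changes will be captured using mixed model analysis of variance for repeated measurement", together with TUDD.

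**The concern.** In this cohort death is the planned end of observation, not a nuisance. Patients have a performance status of 2 or worse, and the required life expectancy starts at 1 month. Censoring a patient who dies without a recorded drop treats that patient as still able to deteriorate later, at the rate of those still under follow-up. The TUDD curve would then be reported as the share of patients who deteriorate, which it is not.

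Patients who die before the first monthly form have a last QoL form that predates the TUDD clock, so they contribute no time. They are the patients closest to death, and so the most relevant to the study's question.

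Objective 5 asks for a length of time before death. The Background section says the palliative period can range from a few days to a few months, so patients at the same time since entry are at very different distances from death. A curve that starts at randomization mixes them.

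**Working it through.** The article gives no event rate, median or power for TUDD or objective 5, so there is no stated figure to reproduce. All rates below are assumptions chosen to show direction and size.

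**Step 1: who is censored.** Setting the event and censoring rules side by side:
- death after a recorded, unreversed drop of at least 5 points: event, reading death as drop-out after a decrease;
- death with no recorded drop: censored at the last QoL form;
- death before the first monthly form: the last form is the baseline or retest, before randomization, so no time is contributed.

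**Step 2: independent constant hazards.** Let the median time to deterioration be 3 months and median survival be m months, so λd = ln2/3 and λm = ln2/m. Then:
- 1-KM = 1 − exp(−λd·t)
- cumulative incidence = λd/(λd+λm) × [1 − exp(−(λd+λm)t)]
- deterioration-or-death = 1 − exp(−(λd+λm)t)

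For m = 2 at t = 3: λd = 0.231 and λm = 0.347. The composite is 1 − exp(−1.733) = 0.823, and the cumulative incidence is 0.4 × 0.823 = 0.329.

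| Median survival (months) | Month | 1-KM | Cumulative incidence | Deterioration or death |
|---|---|---|---|---|
| 2 | 3 | 0.50 | 0.33 | 0.82 |
| 3 | 3 | 0.50 | 0.38 | 0.75 |
| 6 | 3 | 0.50 | 0.43 | 0.65 |
| 2 | 6 | 0.75 | 0.39 | 0.97 |
| 3 | 6 | 0.75 | 0.47 | 0.94 |
| 6 | 6 | 0.75 | 0.58 | 0.88 |

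The value of 1-KM does not move with mortality, while both quantities a reader would want do.

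**Step 3: monthly forms.** In a simulation of 100,000 patients per scenario with the same rates, forms at whole months while alive and censoring at the last form, 1-KM at month 3 stays at 0.50. The share with a deterioration actually recorded by month 3 is 0.27, 0.33 and 0.41 for median survival 2, 3 and 6 months. These shares omit real deteriorations followed by death before the next form, so the fair comparators for 1-KM are the cumulative incidences in Step 2.

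**Step 4: decline tied to death.** The same simulation, with deterioration starting a mean of 0.5, 1 or 2 months before death (exponential lead), at month 3:

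| Median survival (months) | 1-KM by mean lead 0.5 / 1 / 2 months | True deterioration by mean lead 0.5 / 1 / 2 months |
|---|---|---|
| 2 | 0.36 / 0.50 / 0.64 | 0.70 / 0.74 / 0.79 |
| 3 | 0.26 / 0.38 / 0.51 | 0.55 / 0.60 / 0.66 |
| 6 | 0.14 / 0.22 / 0.32 | 0.33 / 0.37 / 0.43 |

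Here 1-KM understates, because many declines fall between the last form and death and the patient is censored.

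**Step 5: patients with no TUDD time.** With exponential survival, the share dying before month 1 is 1 − 2^(−1/m): 0.29 for m = 2, 0.21 for m = 3 and 0.11 for m = 6. These are illustrative upper-end values. Eligibility requires a life expectancy of at least 1 month, which should lower early mortality.

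**Step 6: objective 5.** The objective needs a duration that ends at death. TUDD gives a duration that begins at randomization. The mixed model tests a time trend, but no time scale anchored on death is stated, nor any rule for turning a trajectory into a period. The pattern-mixture groups (no missing score, intermittent, drop-out) do not supply one either.

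**The case against.** Several points on the other side stand.

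- A reader might infer that every death is censored. That is not so: a death after a recorded, unreversed drop is an event.
- A reader might infer that the plan overstates deterioration. Only the comparison in Step 2 with cumulative incidence shows that. The same 1-KM lies below deterioration-or-death, and under the terminal decline that item 5 itself expects for physical dimensions it falls short of the truth (Step 4). With independent hazards, 1-KM correctly estimates a net probability with death removed. The fault there is the target, not informative censoring.
- A reader might infer that the hazard ratios are distorted. No such bias has been shown. Log-rank and Cox results with death censored can be read as cause-specific, which is a legitimate target.
- The sentence on immediate censoring might be read as covering early deaths. It concerns patients with no scores at all, whereas randomized patients have already completed test and retest. Early deaths fall under the last-follow-up rule, with much the same practical effect.
- A reader might infer that objective 5 cannot be estimated. The data allow it, since forms are collected monthly until death and can be re-indexed backward.
- Non-random missingness is addressed for the mixed models, by pattern-mixture models and optional extreme-score imputation.

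It can also be said that an analysis plan will follow and could set the time scale. That answers part of the objective 5 point. It does not answer the TUDD point, because the article already fixes the estimator, the origin and the censoring rule.

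**Conclusion.** The point holds in a limited form. In a cohort followed until death, the stated TUDD rule gives a curve that is not the probability of deterioration. The sign of the error depends on the target and on how closely decline precedes death. At month 3, under the independent-hazard assumptions, 0.50 would be reported against a cumulative incidence of 0.33 to 0.43 and a composite of 0.65 to 0.82. With terminal decline, the reported value could be, for example, 0.38 against 0.60 (median survival 3 months, mean lead 1 month). All of these rest on assumed rates. For objective 5, the stated analyses do not produce an end-of-life period. Only secondary objectives are touched. This should be changed, but it does not threaten the main result.

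**What to change.** **TUDD.** Make the main summary the cumulative incidence of definitive deterioration with death as a competing event, and report deterioration-or-death alongside it. Use the date of death for every patient who dies, including those who die before the first follow-up form. Keep the present censoring rule as a sensitivity analysis, and describe Cox and log-rank results as cause-specific.

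**Objective 5.** Model each QoL dimension against time before death, and prespecify the rule that turns the trajectory into a period. A change-point is one example; other definitions are possible.

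**Cost.** Wording in the analysis plan and some analysis time. No additional assessments are needed, since follow-up already runs to death. The article says the plan is to be written before database lock and reports 12 of 372 patients included, so there is time. There are two drawbacks. Patients alive at database lock do not contribute to the backward-time model. Monthly forms limit its resolution, and patients with short survival will supply few points.
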